### Assessment Instruments

#### Psychopathology

The Positive and Negative Syndrome Scale (PANSS, administration time = 30’) will be used for the evaluation of positive, negative and disorganized symptoms (70). The PANSS is a semi structured interview composed of 30 items divided in three subscales, namely positive symptoms, negative symptoms, and general psychopathology. Each item is accompanied by a specific definition and by detailed anchoring criteria for each rating point, ranging from “absent” (1) to “severe” (7) (71, 72).

The negative symptom subscale includes items which assess cognitive functions and disorganization, therefore only the core negative symptoms will be included in the summary score according to the recently published European Psychiatric Association (EPA) guidance paper on the assessment of negative symptoms (71).

#### Neurocognitive Functions

Neurocognitive functions will be assessed using the Measurement and Treatment Research to Improve Cognition in Schizophrenia (MATRICS) Consensus Cognitive Battery (MCCB) (73–75). This test includes items designed to evaluate seven cognitive domains: (a) processing speed; (b) attention and vigilance; (c) working memory; (d) verbal learning and memory; (e) visual learning and memory; (f) social cognition; (g) reasoning and problem solving (administration time = 80’). The MCCB includes 10 neuropsychological tests (Category Fluency—Animal Naming; Brief Assessment of Cognition in Schizophrenia Symbol Coding; Trail Making Test—Part A; Continuous Performance Test—Identical Pairs; Wechsler Memory Scale Spatial Span; Letter-Number Span; Hopkins Verbal Learning Test—Revised; Brief Visuospatial Memory Test—Revised; Neuropsychological Assessment Battery—Mazes; Mayer-Salovey-Caruso Emotional Intelligence Test) (73, 74). General cognitive abilities will be evaluated with the short form of the Wechsler Adult Intelligence Scale-Revised (WAIS-R). The short form of the WAIS-R uses four subtests (arithmetic, block design, picture completion, and information) to estimate verbal and performance IQ that are highly correlated with the full WAIS assessments (76).

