The present protocol aims to evaluate the efficacy of the integrated SoCIAL program in a large sample of individuals with schizophrenia-spectrum disorders. The program will be administered individually and will include the *narrative enhancement* module, specifically developed to target metacognitive abilities to recognize and integrate mental states, such as emotions, desires, attitudes and goals in real-life situations. The efficacy of the program will be evaluated by comparing the participants randomized to SoCIAL with those randomized to treatment as usual (TAU). The use of the TAU control was deemed appropriate as the study is an early phase trial in which an active control condition including different treatment components may reduce power and increase type II error (68).

The study aims to compare the efficacy of the SoCIAL program vs. TAU in subjects with schizophrenia or schizoaffective disorder (based on DSM-5 criteria) with illness durations < 10 years. The primary outcome is the improvement of social cognition and real-life functioning; while the secondary outcome is the improvement of negative symptoms, functional capacity and neurocognition.

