#### Social Cognition

To better assess social cognition (in addition to the social cognition test included in the MCCB) participants will be administered the Facial Emotional Identification Test (FEIT, administration time = 15’), as well as The Awareness of Social Inference Test (TASIT, evaluation time = 45’), an emotion processing and ToM measure. The FEIT involves black-and-white photographs of 19 different individuals’ faces (nine females/10 males) each depicting one of six different emotions (happiness, sadness, anger, surprise, fear, shame), shown one at a time for 15 seconds (77). After each stimulus, the participant should select which of the six emotions better describe the picture shown (78). The Awareness of Social Inference Test (TASIT) is a measure of basic emotion perception (section “Introduction”) and complex social cognition (ToM in simple and complex interpersonal situations involving sarcasm and deceptions). This test evaluates social cognition through videotaped vignettes designed to reflect real life interactions in different contexts, including free time and work situations (79, 80).

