## Conclusion

SoCIAL is an individualized rehabilitation intervention, specifically designed to improve SC and metacognitive abilities in patients with schizophrenia or schizoaffective disorder. Therefore, this program is meant to train only SC and metacognition, leaving out the other cognition domains. In the recent literature it is still debated whether a combined intervention (i.e., that trains neurocognition using a cognitive remediation training, CRT, along with SC) (89) is better than SC training, as the combined intervention leads to greater improvements in different cognitive domains and in social cognition than CRT alone, a recent meta-analysis indicates that CRT does not enhance the effects of SC training (53). In our opinion, these results (53, 89) indicate unambiguously that the active ingredient to improve social cognition is SCT. Our program consists of two modules: 1) a module that trains emotion recognition and ToM and 2) a module that trains the narrative abilities, focused on metacognition. The SoCIAL program is the first intervention that trains both SC and narrative abilities in subjects with schizophrenia or schizoaffective disorder. To our knowledge, very few studies investigated the effect of narrative enhancement in this population of patients (64–66). In particular, this program, compared to others, shows some peculiarities in narrative enhancement. Firstly, it will be administered individually (not in a group setting); the individual setting allows the possibility of exploring individual experiences and possible difficulties in understanding one’s own emotions in relation to that experience. Secondly, in different narrative enhancement programs patients are asked to write and share stories regarding their illness. The goal of these interventions is to reduce the self-stigma associated with the disease. In SoCIAL, instead, patients are allowed to pick up a topic of their choice for the narrative enhancement training, including those related to internalized stigma. The goal is to train narrative abilities focusing on developing metacognitive skills in integrating internal experience and mental states with behavior in a coherent narrative. The module is added to transfer therapeutic gains of the SCT to real-life functioning. The SCT and narrative enhancement are expected to potentiate each other in developing emotion recognition and ToM skills and to develop narrative abilities.

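### Neurocognition, a secondary outcome, is assigned to the full seven-domain MCCB, which includes the social cognition that the programme trains

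*Protocol article*

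**What the plan says.** All references are to the protocol article.

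- **Introduction (aims).** Social cognition is part of the primary outcome, together with functioning in daily life. Neurocognition is placed one level down: "the secondary outcome is the improvement of negative symptoms, functional capacity and neurocognition". The two are thus separate outcomes at different levels.
- **Neurocognitive Functions.** Neurocognition is to be assessed with the MCCB. "This test includes items designed to evaluate seven cognitive domains", and the list closes with "f) social cognition; (g) reasoning and problem solving". The ten component tests include an emotional intelligence test. No domain or test is set aside.
- **Social Cognition.** FEIT and TASIT are given "in addition to the social cognition test included in the MCCB", so that MCCB test is treated here as a measure of social cognition.
- **Conclusion.** "this program is meant to train only SC and metacognition, leaving out the other cognition domains".
- **Limitations.** Only FEIT and TASIT are named as the trial's social cognition measures.
- **Psychopathology.** The PANSS negative score is restricted to core negative symptoms, because the subscale also holds items on cognition and disorganization.
- **Data Analysis.** Repeated-measures ANOVA, before and after the intervention. No rule is given for scoring the MCCB.

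**The concern.** One test has been placed under two constructs that the trial wants to keep apart. It measures what the programme trains, yet it sits inside the measure of what the programme is said to leave out.

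A neurocognition benefit in this trial would naturally be read as transfer to attention, memory, speed and the like. If the battery is used as described, part or all of such a benefit could be the expected social cognition effect showing through domain (f). If the training works, the error runs one way, towards an apparent neurocognitive gain. The primary comparison, the sample size and the randomisation are not affected. What is at stake is the interpretation of one secondary outcome.

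**Working it through.** **The plan's own figure.** The only design figure is a required total of 68 at power 0.8 and significance level 0.05. The effect size behind it is not stated, so it cannot be reproduced forwards. Solving backwards for 34 per arm, two-sided (an assumption):

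d = sqrt(2/34) × (1.960 + 0.842) = 0.68 by the normal approximation, or 0.69 by the t-test.

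The point does not depend on 68. I use 0.69 only as the upper end of a plausible range for the social cognition effect.

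**Inputs from the article.** Seven MCCB domains, one of them social cognition; 40 per arm (Subjects); repeated-measures ANOVA. With two time points, the group-by-time test is equivalent to a t-test on change scores.

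**Assumptions, none from the article.** Neurocognition is scored as an equally weighted mean of the seven domains; there is no effect on six of them; the social cognition effect d is 0.3 to 0.69 in SD units of the scale on which the test is made; a common inter-domain correlation r on that scale is 0.3 to 0.5; the test is two-sided at 0.05; there is no dropout.

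**Formulas.**

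- Shift of the seven-domain mean = d/7
- SD of the mean = sqrt((1 + 6r)/7)
- Composite effect = (d/7) / sqrt((1 + 6r)/7)

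**Results.** The last column is the power of a two-sample t-test with 40 per arm at the composite effect.

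| d | r | d/7 | SD of mean | Composite effect | Chance of p < 0.05 |
|---|---|---|---|---|---|
| 0.30 | 0.5 | 0.043 | 0.756 | 0.057 | 5.7% |
| 0.50 | 0.4 | 0.071 | 0.697 | 0.102 | 7.4% |
| 0.69 | 0.5 | 0.099 | 0.756 | 0.130 | 8.9% |
| 0.69 | 0.4 | 0.099 | 0.697 | 0.141 | 9.6% |
| 0.69 | 0.3 | 0.099 | 0.632 | 0.156 | 10.6% |

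The range is about 6% to 11%, against a nominal 5%.

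**Sensitivity to r.** A lower correlation raises the figure. At d = 0.69, r = 0.2 gives 12%, and r = 0, which lies well outside the assumed range, gives 21%.

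**After the fix.** With the six non-social domains, a gain confined to social cognition shifts the score by 0 and the rate returns to 5%.

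**If domains are reported one by one.** No average is shifted and the other six domains are untouched. Domain (f) would then appear at its full effect, but in the neurocognition results.

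**The case against.** **The article plans no MCCB composite, and battery scoring belongs in the analysis plan.** This stands as regards size: the percentages above are conditional on a score that the article does not name. It does not remove the point. The assignment of an instrument to a construct is made in the article, and one test is assigned to two. Nor is domain-by-domain reporting secured. The domains to which the Data Analysis section refers back are the neuropsychological, psychopathological and cognitive functioning evaluations, not MCCB domains (a) to (g).

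**The authors clearly distinguish the two constructs.** The Introduction describes neurocognition by attention, memory and learning and contrasts it with social cognition. The list under Neurocognitive Functions can be read as a description of the published battery. That is a fair account of intent, but no exclusion follows from it. Where the authors wanted one, for the PANSS negative score, they wrote it down.

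**A reader might infer that the same effect is counted twice, once in the primary outcome and once in the secondary.** The article does not support this. The Social Cognition section suggests that the MCCB test belongs with FEIT and TASIT, but Limitations names only those two, and no section lists the instruments that form the primary outcome. The point does not need the double count: the MCCB test measures the trained construct whichever tests are primary.

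**A reader might also compute a much larger false-signal rate, up to 34%.** That follows from treating 0.69 as a gain in raw-score SD and dividing by sqrt(2 × (1 − 0.9)) = 0.447 for a pre-post correlation of 0.9. The arithmetic is correct, but 0.69 was solved back from the sample size as an effect on the tested scale. Rescaling it again implies a social cognition effect of 0.69/0.447 = 1.54 change-score SD, far above what the design implies. Kept on the tested scale, 0.69 gives 9% to 11%.

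**Conclusion.** The point holds in a limited form. As written, neurocognition is measured by a battery that contains the trained construct, so a social cognition gain can be reported as a neurocognition benefit.

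The direction is clear if the MCCB is used without exclusion. The size is modest: about 6% to 11% instead of 5%, resting on the equally weighted mean, 40 per arm, no effect on the other six domains, and the assumed effects and correlations. With single-domain reporting there is no such inflation of the other domains, only a misplaced label. Whether the MCCB test also counts towards the primary outcome is unclear, because two sections of the article differ. This is a matter of interpreting a secondary outcome and does not threaten the trial's main comparison.

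**What to change.** In the outcome definitions or the Data Analysis section:

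1. Define the neurocognition outcome as the six MCCB domains other than social cognition.
2. Report the MCCB social cognition test only under social cognition.
3. Reconcile the Social Cognition section with Limitations by stating whether that test belongs with FEIT and TASIT in the primary set.
4. Give any seven-domain MCCB score descriptively only.

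The cost is a sentence or two, settled before the data are analysed. No new data, visits or participants are needed, and the full battery is still administered. The change follows the principle already applied to the PANSS negative score.

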#### Social Cognition

To better assess social cognition (in addition to the social cognition test included in the MCCB) participants will be administered the Facial Emotional Identification Test (FEIT, administration time = 15’), as well as The Awareness of Social Inference Test (TASIT, evaluation time = 45’), an emotion processing and ToM measure. The FEIT involves black-and-white photographs of 19 different individuals’ faces (nine females/10 males) each depicting one of six different emotions (happiness, sadness, anger, surprise, fear, shame), shown one at a time for 15 seconds (77). After each stimulus, the participant should select which of the six emotions better describe the picture shown (78). The Awareness of Social Inference Test (TASIT) is a measure of basic emotion perception (section “Introduction”) and complex social cognition (ToM in simple and complex interpersonal situations involving sarcasm and deceptions). This test evaluates social cognition through videotaped vignettes designed to reflect real life interactions in different contexts, including free time and work situations (79, 80).

#### Functional Capacity and Real-Life Functioning

Functional ability will be assessed by the brief version of UCSD Performance-based Skills Assessment (UPSA-Brief, administration time = 15’), an instrument that measures participants’ capacity to perform tasks similar to those encountered in daily life (81–83). The UPSA-B consists of two of the five subscales from the full UPSA: (1) Financial skills and (2) Communication skills. For the assessment of financial skills, participants are given tasks matching everyday life situations (for example, they are asked to count change or are asked to pay bills). Assessment of communication skills involves tasks in which participants use a disconnected landline telephone to simulate phone calls (e.g., to the doctor’s office) to communicate necessary information. The final score (calculated by summing the two subscale scores) ranges from 0 to 100, with higher scores indicating better functional capacity (81). The Specific Level of Functioning Scale (SLOF, administration time = 20’) will be used to evaluate the subject’s functioning (10). This scale consists of 43 items and relies on data reported by a caregiver or a caseworker of the examined subject (selected on the basis of their familiarity with the subject) and based on the direct observation of subject’s behavior and functioning in several domains: (1) physical functioning, (2) personal care skills, (3) interpersonal relationships, (4) social acceptability, (5) activities of everyday life and (6) work skills (10). Quality of life will be measured through the Quality of Life Scale (QoLS, administration time = 15’), a semi-structured interview, composed by 21 items, designed to assess four different areas of psychosocial adjustment, including Interpersonal Relations, Instrumental Role (e.g., work, school, homemaker), Intrapsychic Foundations (e.g., motivation, sense of purpose), and Common Objects and Activities (e.g., owning a watch, use of public transportation) (84).

### Individualized Cognitive Remediation Program (SOcial Cognition Individualized Activities Lab, SoCIAL)

The SoCIAL program will be administered once a week, for a total of 10 weeks. Each session consists of two different modules: (1) a training program that helps patients recognize emotions and important social signals (such as facial expressions and prosody) and develop strategy focused on the ToM; (2) the *narrative enhancement* module to train metacognitive abilities. Time of administration for both modules is 30 min; the operator, however, can choose to focus the session on one module rather than the other, based on the subject’s specific needs.

Hereafter the description of the two modules.

#### Social Cognition Training

The Emotions recognition training will train the subject’s ability in discriminating between different emotional states; it consists of two sessions for each basic emotion (10 sessions total): fear, anger, surprise, sadness and joy. Educational materials (photos and videos) are used to illustrate prototypical elements of each emotion (facial micro expressions, prosody, gestures etc.) (56). Patients are trained to identify signs of facial emotions using both static faces (photographs) (Figure 1) and dynamic situations (videos) (Figure 2). Lastly, patients will be presented faces with ambiguous emotion expressions and they will be trained in emotions recognition using video footage of daily activities characterized by ambiguous emotional activations.

**FIGURE 1 F1:**
[figure not shown]
Facial emotion recognition material. From top left to top right: increasing intensity of disgust in a woman face; from bottom left to bottom right: increasing intensity of rage in a man face.

**FIGURE 2 F2:**
[figure not shown]
Frames of social interaction’s videos.

The ToM training will help subjects discriminate between emotional expressions in social contexts and understand other people’s mental state (the ability to figure out what other people think and feel in social situations in different contexts, such as work or interpersonal). The ToM training consists of 10 sessions. In each session subjects will watch videos (Figure 3) that display actors expressing one of the following: sarcasm, disappointment, hostility, misunderstanding, deceit and sincerity. The subject will be trained to recognize the feelings, intentions and meaning of the actors’ behaviors in the videos, based on their facial expression, tone of voice and gestures (56). This module uses videos representing social interactions that are increasingly difficult to understand. These tasks will require higher abilities compared to the emotion recognition training, considering that subjects have to integrate verbal and non-verbal emotional data as well as comprehend other people’s mental states in different social situations (e.g., use of the sarcasm in interpersonal work situations).

**FIGURE 3 F3:**
[figure not shown]
Study flowchart: TAU: treatment as usual.

Further information about how the training material was developed can be found in Palumbo et al. (56).

#### Narrative Enhancement Module

The narrative enhancement training is based on the assumption that subjects with schizophrenia show a wide range of impairments in self-awareness, self-reflection, and narrative abilities (64–66, 85–88). The narrative enhancement training in the SoCIAL program consists in story-telling exercises focused on improving the subject’s capacity to comprehend his/her emotional experience and integrate emotions and behavior in real-life situations. The operator uses a semi-structured interview procedure. In the first phase, he asks the patient to share a personal story that makes him/her suffer (e.g., Do you want to tell me a personal story that makes you suffer?). After collecting the story, in a second phase, the therapist clarifies with the patient the specific emotions that the patient feels/has felt in relation to the story (e.g., While you were living this experience, what emotions did you feel? Now how do you feel reliving this experience?). In the third and final phase, the therapist and patient question the emotions felt and whether these emotions can influence the patient’s actions even in the immediate present or in the near future (e.g., Is it possible that feeling inadequate at that party led you to avoid other similar situations?).

### Treatment as Usual

Subjects that will be randomized in this group will receive their TAU for the whole length of the study. TAU includes all the ongoing psychiatric therapies (pharmacological, psychological, occupational, etc.) that subjects may have begun before study’s enrollment.

The number of therapy hours will be recorded and will represent a covariate in group comparisons.

### Length of the Study

The study will have a total length of 12 months, divided in the following phases.

Phase 1. Operators will be trained in evaluating neurocognitive functions, social cognition, functional capacity and real-life functioning. Phase 2. Different operators will be trained in SoCIAL program’s practice. Phase 3. Recruitment of patients and randomization (in both centers). Phase 4. Assessment of neurocognitive functions, social cognition, functional capacity and real life functioning for enrolled patients. Phase 5. Implementation of the interventions. Phase 6. Assessment of neurocognitive functions, social cognition, functional capacity and real life functioning in subjects at the end of the program for both groups (SoCIAL program vs. TAU). Phase 7. Final evaluation and data analysis.

The study’s timetable is shown in Table 1 and the flowchart in Figure 3.

**TABLE 1 T1:** Time schedule of the study.

	Enrollment	Pre-therapy assessment	Allocation	Intervention	Post-therapy assessment
**Enrollment**					
SCID 5	X				
WAIS-R	X				
Informed consent	X				
Randomization					
Allocation			X		
**Intervention**					
SoCIAL				X	
TAU group					
